#### Secondary endpoints

Secondary evaluation criteria are: quality of life assessed by the Short Form 12-item (SF12) scale [28] at 1, 3 and 6 months; time to surgical treatment during the first 6 months (censored criteria); rate of surgical treatment of the CSDH at 1, 3 and 6 months; functional scales: daily living (Instrumental Activities of Daily Living; IADL) [29], cognitive (Mini-Mental State Examination; MMSE) [30] and the modified Rankin Scale [31] at 1, 3 and 6 months; plasma sodium, potassium and fasting glucose at days 0, 7, 14 and 21 and at 1 month; occurrence of adverse events potentially related to methylprednisolone (electrolyte disorders: hypokalemia, metabolic alkalosis, sodium retention (edema), hypertension, congestive heart failure; endocrine and metabolic disorders: Cushing’s syndrome, adrenal insufficiency, glucose disorders (impaired glucose tolerance, diabetes); gastrointestinal disorders: ulcer, perforation, gastrointestinal tract hemorrhage; skin disorders: acne vulgaris, purpura, hematoma, hypertrichosis; neuropsychological disorders: euphoria, insomnia, agitation, confusion, depression; ophthalmological disorders such as glaucoma); survival at 6 months; radiological improvement, defined by reduction of maximal thickness of hematoma and reduction of midline shift evaluated at 1, 3 and 6 months.

Subgroup analyses of all study endpoints will also be performed in subacute (less than 4 weeks old) and chronic (more than 4 weeks old) CSDH, and in patients treated or not treated with anticoagulant or platelet antiaggregant therapy.

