### Study population

Our hypothesis is that 80% of the patients taking placebo will be operated on at 1 month. A total sample size of at least 202 patients (142 events) is required to achieve 90% power to detect a decrease in the rate of surgery to 60% (hazard ratio of 1.756) with methylprednisolone, using a two-sided log-rank test with a 0.05 significance level assuming that the hazards are proportional (nTerim, V1.1, Statistical Solutions Ltd., Cork, Ireland).

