### Measures

#### Screening phase

The screening phase takes place during the hospitalization or consultation in a neurosurgical unit during which the diagnosis of CSDH is confirmed. A standard clinical examination is performed to ensure that the patient meets the selection criteria of the study. The initial CT scan (performed onsite or in another hospital depending on the origin of the patient) completes this initial patient screening. If the patient is eligible, written informed consent from the patient or a representative (if the patient’s cognitive state does not allow informed decision) is necessary before enrollment.

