#### Follow-up

Patients are followed up for a period of 6 months, and are evaluated at 1, 3 and 6 months. At days 0, 7, 14 and 21 and at the 1-month visit, plasma sodium, potassium and fasting glucose are measured. Fasting plasma cortisol at 8 a.m. is measured 2 days after the end of the treatment with corticosteroids (at day 23). Patients will undergo interval cerebral CT scans to evaluate their CSDH at the following intervals: screening visit, M1, M3 and M6 (Fig. 1). This biological surveillance allows the detection of any electrolyte or glycemic impairment that could occur with steroid treatment.

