### Statistical analysis

Statistical analysis will be performed on all evaluated patients (intention-to-treat analysis in the methodology/biometrics unit of the Clinical Investigation Centre Inserm 1414 of Rennes. The statistical significance will be considered to be *p* values < 0.05 for all analysis.

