#### Analysis of other criteria

Student’s *t* test or a Mann-Whitney test if necessary will be used to compare quantitative variables. Quantitative criteria evaluated several times during the monitoring will be compared with repeated measures analysis of variance (ANOVA) with two factors (time, group). For qualitative criteria, a chi^2^ test will be used. For all these analyses, adjustments can be made in case of heterogeneity at inclusion.

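### Radiological improvement is defined as any reduction, and the protocol does not say whether it is tested yes/no or in millimetres; the yes/no route would cost power on this secondary endpoint

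*Protocol article*

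**What the plan says.** Protocol article, Secondary endpoints: the radiological criterion is "radiological improvement, defined by reduction of maximal thickness of hematoma and reduction of midline shift evaluated at 1, 3 and 6 months". No minimum change is given. The text does not say whether thickness and shift must both fall or are assessed separately, and it does not name the reference scan.

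Protocol article, Follow-up: CT is scheduled at "screening visit, M1, M3 and M6", so the screening scan is the only pre-treatment scan listed and the natural reference. Under Screening phase, "The initial CT scan (performed onsite or in another hospital depending on the origin of the patient) completes this initial patient screening".

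Protocol article, Analysis of other criteria, gives two routes:
- One suits a yes/no outcome: "For qualitative criteria, a chi^2^ test will be used".
- The other suits a measurement repeated over visits: "Quantitative criteria evaluated several times during the monitoring will be compared with repeated measures analysis of variance (ANOVA) with two factors (time, group".

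The section does not say which route radiological improvement takes. It allows adjustment only as an option, if the arms turn out to differ at inclusion.

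**The concern.** An improvement that is defined by a condition reads naturally as a status the patient has or lacks, and such a status would go to the chi-square test. On that reading a fall from 20 to 19 mm counts the same as a fall from 20 to 0 mm. Later in follow-up, when nearly every hematoma is at least slightly thinner, both arms approach 100% and the criterion can hardly separate them. A real steroid effect on hematoma size could then be missed, although the measurements that would show it have been taken.

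The other reading, a comparison of millimetres, fits the ANOVA sentence equally well. The two routes differ materially in power, so the protocol should say which one applies.

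**Working it through.** **The plan's own figure.** The protocol gives no response rate, effect size, reading error or power for the radiological endpoint. Its only sample size is for the primary endpoint, and it reproduces:
- Hazard ratio = ln(0.20)/ln(0.40) = 1.756.
- Freedman events = (1.960 + 1.282)² × (2.756/0.756)² = 10.51 × 13.29 ≈ 140.
- Patients = 140/0.70 = 200, close to the stated 142 events and 202 patients.

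From this the check takes n = 101 per arm. The protocol applies p "values < 0.05 for all analysis"; two-sided testing is carried over from the primary endpoint ("using a two-sided log-rank test with a 0.05 significance level").

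**Assumed inputs (none from the documents).** Extra mean reduction on active 2 mm; between-patient SD of true change 5 mm; reading SD e per scan of 0, 1 or 2 mm; mean placebo reduction m of 0, 3, 6 or 9 mm; normal changes; every patient scanned.

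**Formulas.**
- SD of observed change: s = √(25 + 2e²), which is 5.00, 5.20 and 5.74 mm for e = 0, 1 and 2.
- Share reduced: placebo p₀ = Φ(m/s), active p₁ = Φ((m + 2)/s).
- Yes/no power = Φ{[(p₁ − p₀)√n − 1.960√(2p̄(1 − p̄))] / √(p₀(1 − p₀) + p₁(1 − p₁))}, with p̄ the mean of p₀ and p₁.
- Millimetre power = Φ{2/(s√(2/n)) − 1.960}.

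**Worked case, e = 1, m = 0.** p₀ = 0.500, p₁ = 0.650. Yes/no: (0.1498 × 10.05 − 1.960 × 0.699)/0.691 = 0.20, power 58%. Millimetres: 2/(5.196 × 0.1407) − 1.960 = 0.775, power 78%.

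| Mean placebo reduction | Share reduced, e = 1 (placebo vs active) | Yes/no power, e = 0 | Yes/no power, e = 1 | Yes/no power, e = 2 |
|---|---|---|---|---|
| 0 mm | 50% vs 65% | 61% | 58% | 50% |
| 3 mm | 72% vs 83% | 51% | 49% | 43% |
| 6 mm | 88% vs 94% | 34% | 33% | 31% |
| 9 mm | 96% vs 98% | 17% | 18% | 19% |

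Millimetre power is 81%, 78% and 70% for e = 0, 1 and 2, whatever m is. Simulation of 4,000 trials agrees: at e = 1 the yes/no power is 58%, 51%, 34% and 16%, against about 78% in millimetres.

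**Source of the loss.** With no reading noise, yes/no power already runs from 61% down to 17%. Adding noise of SD 1 mm changes it by at most about 3 points. At SD 2 mm and m = 0 it costs about 11 points (61% to 50%), but it costs the millimetre analysis the same (81% to 70%). The loss comes from splitting at zero and from the ceiling.

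**Would a margin above reading error help?** With a margin of 2.77 reading SDs and m = 0, power goes from 58% to 56% (e = 1) and from 50% to 41% (e = 2). At m = 9 and e = 1 the shares become 88% vs 94% and power rises from 18% to 32%, still far below 78%.

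**Fewer evaluable patients.** With an illustrative 50 per arm and e = 1, millimetre power is 49%, and yes/no power is 33%, 27%, 19% and 11%. All figures drop and the ranking stays.

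**The case against.** The strongest objection is that the yes/no test is an assumption. The endpoint list uses the word rate when it means a proportion, as for surgery, and does not do so here. The stated objective concerns how the lesions evolve, and repeated thickness in millimetres is exactly what the ANOVA sentence describes. On that reading no dichotomy arises and most of the remedy is already in place. This stands, and it is why the point is conditional. It does not remove the ambiguity. Nor does the ANOVA sentence commit to adjusting for the screening value, since adjustment is left to depend on imbalance.

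A reader might infer that reading noise scores half of all unchanged hematomas as improved. That holds only for thickness alone on a continuous scale. With readings in whole millimetres it is 26% to 43% (assumed reading SD 0.5 to 2 mm). If thickness and shift must both fall it is about 25% or less, and zero where there is no shift to reduce, which the entry criteria permit. A reader might also infer that noise is what destroys the power, and that a margin above reading error would restore it. The working shows neither is so.

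Other objections limit the size. The protocol expects 60% to 80% of patients to be operated on by 1 month, so 101 unoperated patients per arm with complete scans is optimistic. Thickness also cannot fall below zero, so a constant 2 mm effect becomes less realistic at large placebo reductions. Both affect the absolute percentages.

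Finally, cut-offs and reading rules are commonly left to a full protocol or SAP that is not shown. Their absence is therefore not the point here. The point is that the stated definition fits two analyses of very different efficiency.

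**Conclusion.** The point holds in conditional form. The definition admits any reduction, and the protocol leaves open whether it is analysed yes/no or in millimetres. If yes/no, power is about 58% falling to 16% as the mean placebo reduction rises from 0 to 9 mm, against about 78% for the millimetre change. This assumes a 2 mm effect, between-patient SD 5 mm, reading SD 1 mm and 101 per arm with complete scans. The percentages are illustrative because the documents supply only the 101 per arm; the ranking held at every reading SD and sample size tried.

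The documents do not support saying that the trial has committed to a responder test, or that noise alone invalidates the endpoint. Under blinding, reading error should be similar in both arms, so the risk is a missed effect and not a false positive. The primary endpoint and the 202 patients are unaffected. This is a minor improvement to one secondary endpoint.

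**What to change.** State in Analysis of other criteria that maximal thickness in millimetres at 1, 3 and 6 months is analysed as a quantitative endpoint, adjusted for its screening CT value whether or not the arms differ at inclusion. Name the screening CT as the reference in the definition. If an improvement rate is kept, label it descriptive, and say whether both thickness and midline shift must fall.

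The cost is wording only: the scans are already scheduled and the endpoint already rests on maximal thickness. The price is that a simple improvement percentage is no longer the tested quantity. If the full protocol or SAP already specifies the millimetre analysis with baseline adjustment, a sentence pointing to it is enough.

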### Description of the measures taken to reduce and prevent bias

#### Randomization

The randomization list will be prepared by the Biometrics Unit of the Clinical Investigation Centre Inserm 1414 of Rennes. Randomization will be stratified by center and equilibrated at a 1:1 ratio. After verification of selection criteria during the screening phase, the investigator will proceed to the randomization of the patient the day of baseline (D0). The investigator sends the order-processing request to the pharmacist of his center. The pharmacist attributes treatment to the patient according to their list in chronological order and informs the coordinating centre by faxing the completed order.

#### Methods of blinding

This study is double-blind. Active treatment and placebo will be identical and prepared in capsules by an institutional platform of pharmaceuticals production at Brest University Hospital.

### Study population

Our hypothesis is that 80% of the patients taking placebo will be operated on at 1 month. A total sample size of at least 202 patients (142 events) is required to achieve 90% power to detect a decrease in the rate of surgery to 60% (hazard ratio of 1.756) with methylprednisolone, using a two-sided log-rank test with a 0.05 significance level assuming that the hazards are proportional (nTerim, V1.1, Statistical Solutions Ltd., Cork, Ireland).

#### Inclusion criteria

Patients eligible for the study must follow the following criteria: age above 18 years old; with chronic or subacute, uni- or bilateral subdural hematomas; confirmed by cerebral computed tomography (CT) scan without contrast enhancement (an additional CT scan is mandatory for patients with CSDH diagnosed using another imaging modality (e.g., magnetic resonance imaging)); without clinical (Glasgow Coma Scale score ≤12, motor deficit <4/5) and radiological signs of severity (midline shift >5 mm, uncal transtentorial herniation) assessed by the neurosurgeon investigator in charge of the patient; written informed consent from patients or their next of kin according to the patients’ cognitive status.

#### Exclusion criteria

The noninclusion criteria of this trial (one criterion is enough to exclude a patient) are the following: clinical signs of severity (Glasgow Coma Scale score ≤12, motor deficit <4/5); radiological signs of severity (midline shift >5 mm, uncal transtentorial herniation); diabetes mellitus; contraindications for methylprednisolone (uncontrolled infectious disease, evolutive viral disease (e.g., HIV, hepatitis, herpes, varicella, herpes zoster), known psychiatric disorder, known hypersensitivity to methylprednisolone or lactose intolerance); previous surgery for CSDH during the past 6 months; pre-existing severe dementia, defined by a MMSE score <16 related to an etiology other than CSDH; neurological pathology that can be associated with dementia; long-term corticosteroid treatment; patient under legal protection (conservatorship, trusteeship, guardianship) or deprivation of freedom; participation of the patient in other concomitant clinical research studies.

### Treatment administered in the study

#### Identification of treatment

Methylprednisolone will be supplied as a powder and encapsulated in capsules containing 16 mg of drug with lactose as the excipient. Placebo capsules contain only lactose. Capsules will be packaged in boxes of 40. Boxes will be stored in containers of three boxes.

#### Packaging and labeling

Each box of medication for the study is identified by a specific label for a clinical trial in compliance with applicable regulatory requirements including European regulations.

#### Administration

The duration of treatment is 21 days. Capsules are administered orally in the morning, during breakfast. They will be dispensed by a nurse when patients may not be able to take capsules themselves. Prescription dosage is adapted according to the weight of the patient (approximately 1 mg/kg): three 16-mg capsules/day (patient <60 kg), four 16-mg capsules/day (patient 60–80 kg), five 16-mg capsules/day (patient >80 kg).

The treatment duration is supported by the pathophysiology of CSDH formation (inflammatory process supposed to be maximal at 2 to 3 weeks) [4, 8, 9, 11–19].

#### Precautions for use

Because of the potential risk of water retention, hyperglycemia or hypokalemia, the patients will receive written dietetic advice to follow a diet with a low intake of fast-release carbohydrates and salt, and increased intake of potassium, during the treatment period. A specific dietetic form will be drawn up by a dietician before the beginning of the study. In addition to these dietetic measures, specific monitoring of plasma sodium, potassium and glucose will be carried out. Patients will also be informed of all expected steroid side effects and will be advised to contact the investigator in case of suspicion of any adverse effects during the treatment period.

#### Authorized and unauthorized medicinal products

Management of drugs affecting hemostasis (antiplatelet drugs, orally administered anticoagulants and heparin) will be based on the habits of the participating centers in the absence of evidence-based guidelines. Contraindications to medicinal product combinations listed in the Summary of Product Characteristics for methylprednisolone, will be complied with. In addition, clinical and/or close laboratory test monitoring will be applied whenever a potential interaction with a concomitant medicinal product exists.

In case of the failure of treatment with corticosteroids, defined by a lack of clinical improvement, clinical deterioration, immediately or after a phase of improvement, radiological progression or corticosteroid intolerance, surgical treatment should be considered. In case of persistence of the CSDH at the end of the study, its treatment will follow the centre’s normal policy.

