#### Primary endpoint

The primary evaluation criterion is the delay of occurrence of surgical treatment (censored criteria) of the CSDH at 1 month. One month has been chosen for assessing the primary endpoint because most surgical interventions, if needed, are expected to occur during the first month following the diagnosis of CSDH. Patients who are nonevaluable for the primary endpoint (death, loss to follow-up, etc.) will be censored at the date of death or the latest news.

Criteria for recourse to surgery are (one is sufficient): lack of clinical improvement at 1 month, immediate or delayed clinical deterioration, appearance of radiological signs of severity (midline shift >5 mm, uncal transtentorial herniation).

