As mentioned above, one of the weaknesses of our work is the lack in the academic literature of studies describing the natural history of CSDH without treatment; some may claim that some cases of CSDH without clinical and neurological signs of severity could heal spontaneously. Another issue concerns the inclusion of patients with cognitive disorders. Confusion and dementia might be difficult to distinguish in an acute context, so the questioning of the relatives is of particular importance. We still wanted to include patients with doubtful or mixed semiology, who pose the greatest ethical dilemmas in everyday practice. A medical alternative to surgery in these cases would be of particular interest considering the invasiveness of surgery for that fragile population. However, corticosteroids might have psychic side effects liable to destabilize the mental status of such patients.

Another point of debate is the duration of corticosteroid therapy. After discussion with the endocrinology team of our establishment and on the basis of the academic literature [36–39], we decided to limit the treatment to 3 weeks. Indeed, after this period the risk of adrenocortical insufficiency induced after the discontinuation of corticosteroids increases significantly. Usually, adverse effects associated with corticosteroids predominantly occur during consumption of these medications over several weeks or months. We also decided to lower the inclusion boundary to a GCS score of 13. For those patients with a GCS score of 13 and, therefore, mild vigilance disorders, we recommend close monitoring in neurosurgical departments during the first days or the first week of treatment in order to assess the effectiveness of the treatment and possibly perform surgery in case of clinical deterioration. We left the choice to each of the investigators about the choice of timing to perform a secondary surgery.

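### The article gives two different sets of triggers for surgery, which is the primary event, and only one of them includes corticosteroid intolerance; such operations would probably dilute the effect

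*Protocol article*

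**What the plan says.** The event is surgery. Under Primary endpoint: "The primary evaluation criterion is the delay of occurrence of surgical treatment (censored criteria) of the CSDH at 1 month". Analysis of the primary endpoint compares time to surgery between the groups with a log-rank test and does not restrict events by the reason for operating.

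The triggers for that event appear in two places.

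- **Primary endpoint:** "Criteria for recourse to surgery are (one is sufficient): lack of clinical improvement at 1 month, immediate or delayed clinical deterioration", and then "appearance of radiological signs of severity (midline shift >5 mm, uncal transtentorial herniation".
- **Authorized and unauthorized medicinal products:** "In case of the failure of treatment with corticosteroids, defined by a lack of clinical improvement, clinical deterioration, immediately or after a phase of improvement", and then "radiological progression or corticosteroid intolerance, surgical treatment should be considered".

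On timing, the Discussion says: "We left the choice to each of the investigators about the choice of timing to perform a secondary surgery". On masking, Methods of blinding says: "This study is double-blind. Active treatment and placebo will be identical". Identification of treatment adds: "Placebo capsules contain only lactose".

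**The concern.** Because the endpoint is the act of operating, whatever prompts an operation also generates primary events. A centre working from one list and a centre working from the other could handle the same patient differently, and the log-rank test would record different event times or a different event status.

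Intolerance raises a second issue. It reflects a side effect of the drug rather than failure to control the hematoma, and the true form cannot occur on lactose capsules. If it leads to surgery, events may be added unevenly between the arms. At stake are consistency of the endpoint across centres, power, and how easily a null result could be read: as no effect on the hematoma, or as an effect partly offset by operations for intolerance.

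**Working it through.** **Step 1. The two lists side by side**

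| Trigger | Primary endpoint | Authorized and unauthorized medicinal products |
|---|---|---|
| No clinical improvement | judged at 1 month | no time point |
| Clinical deterioration | yes, early or late | yes, early or after improvement |
| Radiology | shift above 5 mm or herniation | any progression, no threshold |
| Corticosteroid intolerance | not listed | listed |
| Force | criteria, one is enough | surgery to be considered |

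They agree on deterioration and differ on the other three triggers. A patient whose hematoma thickens without passing the threshold, or who is clinically stable but intolerant, meets the second list and not the first. The time point matters too. If non-improvement is judged at 1 month, the resulting operation may fall at or after the endpoint's own horizon. With no time point, the same patient could be operated on earlier and be counted.

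**Step 2. Reproduce the plan's figure**

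Inputs from Study population: 80% operated on placebo, 60% on methylprednisolone, two-sided 0.05, 90% power, hazard ratio 1.756, 142 events, 202 patients.

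- HR = ln(1 − 0.80) / ln(1 − 0.60) = 1.756, as stated.
- Freedman events = (1.960 + 1.282)² × [(HR + 1)/(HR − 1)]² = 139.5, rounded up to 140. Dividing by the mean event rate of 0.70 gives 200 patients. This is close to the stated 142 and 202.
- Schoenfeld's formula gives 133 events and 190 patients and does not match, so Freedman is used below.

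**Step 3. Illustrate dilution from operations for intolerance**

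The article gives no intolerance rate, so the added percentage points are an assumption. Placebo is held at 80% with 101 patients per arm. The test level is 0.04626, the value stated for the final analysis (z = 1.993).

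- Events = 101 × (0.80 + p), where p is the active-arm rate.
- HR = ln(0.20) / ln(1 − p).
- Power = Φ( √events × (HR − 1)/(HR + 1) − 1.993 ).

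| Active-arm rate p | Share of otherwise-spared active patients operated on, (p − 0.60)/0.40 | HR | Events | Power |
|---|---|---|---|---|
| 60% | 0% | 1.756 | 141.4 | 0.898 |
| 62% | 5% | 1.663 | 143.4 | 0.839 |
| 64% | 10% | 1.575 | 145.4 | 0.758 |
| 66% | 15% | 1.492 | 147.5 | 0.657 |

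**Step 4. Let suspected intolerance also lead to surgery on placebo**

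Suppose otherwise-spared placebo patients are operated on at half the active-arm share. The placebo rate becomes 80.5%, 81.0% or 81.5%, and power becomes 0.861, 0.813 or 0.756. At one fifth of the active-arm share, in the 5% and 10% rows, power is 0.848 and 0.781.

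**The case against.** Several points on the other side are sound.

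- **The event is not contradictory.** A reader might infer that the primary event itself is defined in two ways. It is not: the endpoint and analysis sections both count any surgical treatment of the hematoma. Only what leads to surgery differs, and the text already implies that an operation for intolerance is an event.
- **The lists differ in force and perhaps in scope.** The second says only that surgery is to be considered, and its paragraph runs on to the end of the study, which may explain the missing time point. This softens the conflict, but nothing tells a centre which list to follow during the first month.
- **The Discussion sentence on timing adds no trigger.** It gives investigators discretion and contradicts neither list.
- **Intolerance need not be confined to the active arm.** A reader might infer that it is. Capsules are identical, all patients are told the expected steroid effects, and several listed effects (insomnia, confusion, hypertension) are not specific to steroids. Only true intolerance is confined to methylprednisolone, so an active-arm excess is probable but its size is unknown.
- **Counting intolerance is a legitimate choice.** The second list classes it as treatment failure, and a patient who cannot take the drug and is operated on has not avoided surgery. A reader might go further and call a null result uninterpretable. The documents do not support that: an intention-to-treat comparison of all operations stays valid, and the distortion, if any, is conservative.
- **The 60% may already include such operations.** The Discussion bases it on the authors' empirical experience with the treatment, so adding points to it could count them twice.
- **Stratification by center** balances local surgical habits between the arms. It does not make the triggers uniform.

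What stands is an unreconciled difference in three triggers for the act that is the primary event.

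**Conclusion.** The concern holds in limited form. The article disagrees with itself on what leads to surgery: the time point for non-improvement, the radiological threshold, and whether intolerance is a trigger. The definition of the event is consistent.

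Operations for intolerance would probably fall more often on methylprednisolone and pull the hazard ratio toward 1. That costs power and does not create a false-positive risk. The size cannot be known from the article. The fall from about 90% to 84%, 76% or 66% is an illustration that assumes 2, 4 or 6 added points on active drug and none on placebo. It shrinks to about 86%, 81% or 76% if placebo has half the active-arm share, and there is no shortfall against the plan if the 60% already includes these operations. The looser radiological and timing wording can add events in both arms, and its net effect is not estimated here. This is worth correcting, but it ranks below a must-fix.

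**What to change.** 1. Reconcile the Primary endpoint section with the section on authorized and unauthorized medicinal products into one list of triggers for all centres, settling the time point, the radiological definition and the place of intolerance. Which clinical rule applies is for the investigators.
2. Record the reason for each operation at the time of surgery, while still blinded.
3. Keep all operations as events in the primary log-rank test.
4. Prespecify one sensitivity analysis in which operations triggered only by intolerance are not counted as events. State how those patients are then handled; if they are censored at the operation, note that the censoring may be informative.

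The cost is a wording amendment, one case report form field and one extra analysis. The stated 142 events and 202 patients need not change.
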